##### Music-Movement Synchronization

Music-movement synchronization is an objective behavioral metric captured by the VR software, reflecting the accuracy and timing of participants’ physical movements relative to musical beats. Within the SDT framework, this variable is treated as an exploratory behavioral indicator that may reflect task engagement and perceived competence. It is not a primary or confirmatory outcome; any associations with other variables will be interpreted as hypothesis generating.

All self-report and fitness measures will be collected at T0, T1, and T2. In-VR behavioral data will be captured continuously during the intervention period.

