### Safety Monitoring and Adverse Events

Adverse events will be monitored throughout the trial. Participants will be asked about dizziness, nausea, eyestrain, disorientation, social distress, and symptom worsening at each VR session and at formal assessment points. The Simulator Sickness Questionnaire (SSQ) will be administered at the end of every VR session to track habituation trajectories and detect differential cybersickness across groups; SSQ scores will be examined as a potential covariate in sensitivity analyses. Sessions may be paused or discontinued if participants experience clinically meaningful discomfort. All adverse events and withdrawals will be recorded.

Predefined clinical thresholds will be used to identify participants requiring immediate attention. A BDI-II total score exceeding 28 (indicating severe depression) or any endorsement of suicidal ideation on BDI-II item 9 (score ≥1) at any assessment point will trigger immediate clinical review. Similarly, a BAI total score exceeding 25 (indicating severe anxiety) will prompt review. Self-report assessments will be scored in real time at each formal assessment point, with automatic flagging of scores exceeding these thresholds. Session facilitators will also conduct a brief verbal check-in before and after each VR session to monitor participant well-being.

When a clinical threshold is met, the session facilitator will immediately notify the principal investigator, who will conduct or arrange a clinical risk assessment within 24 hours. Participants meeting clinical concern criteria will be referred to the psychological counseling center at Hunan Traditional Chinese Medical College for nonurgent concerns or to the psychiatric emergency department at the nearest affiliated hospital for acute crises. The principal investigator ([name]) will serve as the designated safety officer responsible for overseeing all safety monitoring procedures and referral decisions. Participants who are referred for clinical care may continue in the trial if deemed safe by the assessing clinician or may be withdrawn if continued participation poses a risk to their well-being.

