### Data Collection and Analysis

Data collection will be conducted via a secure online survey platform and directly from the VR software. All primary analyses will follow the intention-to-treat principle and will include all randomized participants with available data.

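### Safety withdrawal is written as leaving the trial, without separating the end of VR sessions from the end of outcome assessment, so later BDI-II and BAI scores of participants who worsen may be lost

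*Protocol article*

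**What the plan says.** - **After a referral** (Safety Monitoring and Adverse Events): the participant "may continue in the trial if deemed safe by the assessing clinician or may be withdrawn if continued participation poses a risk to their well-being".
- **Triggers** (same section): a BDI-II total above 28 or any endorsement of item 9 leads to clinical review, and "a BAI total score exceeding 25 (indicating severe anxiety) will prompt review". These are read from questionnaires: "Self-report assessments will be scored in real time at each formal assessment point".
- **Between assessments** (same section): "Participants will be asked about dizziness, nausea, eyestrain, disorientation, social distress, and symptom worsening at each VR session", and facilitators hold a verbal check-in before and after each session. A separate sentence covers discomfort: "Sessions may be paused or discontinued if participants experience clinically meaningful discomfort". All adverse events and withdrawals are to be recorded.
- **Outcome schedule** (end of the Outcomes section): "All self-report and fitness measures will be collected at T0, T1, and T2". BDI-II and BAI have no scheduled assessment between T0 and T1.
- **Analysis** (Data Collection and Analysis; Data Management): the primary analyses follow intention-to-treat and "will include all randomized participants with available data". The model is a random-intercept mixed model fitted by maximum likelihood. Its main contrasts are social versus solo VR at T1 and T2. Multiple imputation and per-protocol analyses are the named sensitivity analyses.

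**The concern.** Stopping a treatment and stopping follow-up are different events, and intention-to-treat depends on keeping them apart. The referral rule merges them: the participant stays in the trial or leaves it. The protocol's own rule can then create missing primary outcomes among people who are doing badly.

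The loss matters most between T0 and T1. Someone withdrawn in that window because a facilitator noticed worsening would contribute only a pre-treatment score. The likelihood fills in the rest from participants who stayed, and it has no record of the worsening that caused the exit.

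The loss could differ between the two arms of the primary comparison. Voice chat, team competition and visible comparison exist only in the social arm, so distress arising from peers is more plausible there. The facilitators who hold the check-ins are not blinded. The trial already expects 20% to 30% attrition.

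**Working it through.** The documents give no figure for this point, so none can be reproduced. The check has two parts: which scores can be lost, and what the planned model does with the loss.

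**1. Which scores can be lost**

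| When concern arises | What is already recorded | What withdrawal can remove |
|---|---|---|
| Score flag at T0 | T0, taken before randomization (Participant Timeline) | not a post-randomization outcome trigger |
| Worsening noticed at a session, T0 to T1 | T0 only | T1 and T2 |
| Score flag at T1 | T0 and T1 | T2 only |
| Score flag at T2 | all three | nothing |

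**2. Inputs**

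- From the protocol: threshold BDI-II > 28; 110 / 3 = 36.7 per arm; f = 0.25, which for two groups is d = 2f = 0.5; random intercept; maximum likelihood.
- Assumed, not in the documents: BDI-II means 21, 17 and 16 at T0, T1 and T2; SD 8 throughout (variant: 5, 8, 8); correlation ρ of 0.5 or 0.7; no true arm difference; and, by arm, the proportion p of those with T1 > 28 who are withdrawn.
- Scale: 0.5 × 8 = 4 points for the assumed effect.

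**3. Withdrawal before T1**

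Share of an arm whose T1 score would exceed 28: P(Z > (28 − 17)/8) = P(Z > 1.375) = 0.0846. Their mean excess over the arm mean at T1: 8 × φ(1.375)/0.0846 = 8 × 0.1550/0.0846 = 14.66 points.

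The model predicts their T1 from T0 alone. It recovers about ρ² of that excess, and it starts from an arm mean that is itself too low. With withdrawn share q = p × 0.0846, the downward bias b in an arm's T1 mean satisfies b = q[(1 − ρ²) × 14.66 + b], so

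b = q(1 − ρ²) × 14.66 / (1 − q).

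| p, social vs solo | ρ = 0.5 | ρ = 0.7 |
|---|---|---|
| 0.50 vs 0.50 | 0 | 0 |
| 0.50 vs 0.25 | 0.486 − 0.238 = 0.25 | 0.330 − 0.161 = 0.17 |
| 0.50 vs 0 | 0.0423 × 0.75 × 14.66 / 0.9577 = 0.49 | 0.0423 × 0.51 × 14.66 / 0.9577 = 0.33 |
| 1.00 vs 0 | 0.0846 × 0.75 × 14.66 / 0.9154 = 1.02 | 0.0846 × 0.51 × 14.66 / 0.9154 = 0.69 |

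These are false benefits, in BDI-II points, for the arm that withdraws more. In people, q = 0.0423 is about 1.6 of 36.7 and q = 0.0846 is about 3.1 of 36.7.

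Large simulations with the random-intercept model agree. Including the variant with SD 5 at T0, the ranges are:

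| p, social vs solo | T1 bias | T2 bias |
|---|---|---|
| 0.50 vs 0.50 | about 0 | about 0 |
| 0.50 vs 0.25 | 0.16 to 0.30 | 0.05 to 0.15 |
| 0.50 vs 0 | 0.33 to 0.54 | 0.16 to 0.33 |
| 1.00 vs 0 | 0.68 to 1.24 | 0.29 to 0.60 |

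A second selection rule gives similar sizes. If withdrawals come from the fifth of the social arm with the worst T0 to T1 change and none come from the solo arm (SD 8, ρ = 0.5), the T1 bias is about 0.4 points at 5% withdrawn (1.8 people) and about 0.9 at 10% (3.7 people).

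**4. Withdrawal after a recorded T1 score**

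Here only T2 is missing, and the reason is in the data. T1 bias is about 0. T2 bias is about 0 when the random-intercept structure is right, even at 1.00 vs 0. With SD 5, 8, 8, where that structure is wrong, unequal withdrawal gives 0.02 to 0.22 points.

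**5. Named sensitivity analyses**

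Standard multiple imputation rests on the same missing-at-random assumption as the main model. A per-protocol analysis would tend to drop these participants. Neither examines loss driven by unrecorded worsening.

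**The case against.** The case for leaving the text alone has real force.

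- **The score thresholds cannot remove T1.** They are applied at formal assessments, so the triggering score is already in the data. This stands. A reader might infer that the worst T1 and T2 scores simply go missing, but the protocol does not support that.
- **Withdrawal before T1 is not spelled out.** The referral steps start when a clinical threshold is met, and the stated thresholds are questionnaire scores. Trouble in a session is answered by pausing or stopping sessions. This stands in part: the route is possible, because worsening is asked about at every session and the rule does not limit withdrawal to score flags, but it is not stated.
- **Withdrawal is not defined as ending assessment, and the outcome schedule has no exception.** This is fair, but the wording contrasts continuing in the trial with being withdrawn, and nothing keeps T1 and T2 going afterwards. The article states a rule here, so this is more than a detail left to a fuller document.
- **Nobody is dropped outright.** A participant with T0 only stays in the mixed model, and all adverse events and withdrawals are recorded. This stands. A reader might infer that harmed participants vanish from the analysis set or from the safety report; they do not.
- **Bias needs unequal withdrawal.** Both VR arms have the same session schedule and the same safety questions. With equal withdrawal the bias is about 0. At SD 8 and 36.7 per arm, a simple difference has standard error 8 × √(2/36.7) = 1.87 points, so the smaller biases are well inside the noise. This stands, and it rules out saying that the comparison is biased.

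**Conclusion.** The point holds in a limited form. The referral rule treats safety withdrawal as leaving the trial and does not separate the end of VR sessions from the end of outcome assessment. T2 scores may be lost for participants who worsen, and T1 scores as well for anyone withdrawn before T1 on worsening seen only at a session.

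The first kind of loss is largely absorbed by the planned model. The second is not, and the named sensitivity analyses do not probe it. If it were more frequent in one VR arm, it would favour that arm by about 0.2 to 0.9 BDI-II points at T1, roughly 5% to 23% of a 4-point effect. The extreme of everyone above 28 withdrawn in one arm and nobody in the other reaches about 1.0 point at SD 8 and 1.2 in the variant. All of this rests on assumed means, SDs, correlations and withdrawal rates. The documents do not show that withdrawal will be unequal, so the comparison may be biased, not that it is.

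The change is worth making because the outcomes are online questionnaires, sizeable attrition is already expected, and recruitment had not begun as of April 2026.

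**What to change.** Leave the clinical decision on who stops, and the clinician's option to end participation, exactly as they are. Add a data-collection rule to Safety Monitoring and Adverse Events, with a matching line in Data Collection and Analysis:

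*Participants who are stopped from VR sessions or withdrawn on safety grounds will still be asked to complete the online BDI-II and BAI at T1 and T2, unless they withdraw consent to data collection or the assessing clinician advises against contact. These data enter the intention-to-treat models in the group to which the participant was randomised.*

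To the extent that these scores are obtained, the loss by this route and its bias disappear. The cost is a few extra follow-up contacts and matching wording in the consent form.

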### Data Collection and Analysis

Data collection will be conducted via a secure online survey platform and directly from the VR software. All primary analyses will follow the intention-to-treat principle and will include all randomized participants with available data.

### Data Management

All data will be entered into a secure electronic database with verification procedures. Identifiable information will be stored separately from outcome data on encrypted institutional servers, accessible only to authorized members of the research team.

For the primary outcomes, linear mixed-effects models will be used to examine group, time, and group×time effects on BDI-II and BAI scores. Separate models will be fitted for depression and anxiety outcomes, with participant-level random intercepts to account for repeated measures over time. Gender and primary presenting concern (the stratification variables) will be included as covariates, and baseline symptom severity will be considered in model specification as appropriate. The primary planned contrasts will compare the experimental group with the active control group at T1 and T2; comparisons involving the waitlist control group will be secondary and should be interpreted with caution, given the expectancy and novelty confounds inherent in waitlist comparisons. Post hoc pairwise comparisons will be adjusted for multiple testing using a Holm procedure. Secondary outcomes will be analyzed using analogous mixed-model approaches. Cybersickness (SSQ scores) will be examined as a potential covariate in sensitivity analyses to assess whether differential simulator sickness across groups confounds the primary results. Missing data assumptions will be examined, with maximum likelihood estimation in mixed models as the primary approach and multiple imputation and per-protocol analyses used as sensitivity analyses where appropriate. Exploratory analyses will examine whether changes in Basic Psychological Need Satisfaction Scale scores are associated with changes in BDI-II and BAI scores and whether music-movement synchronization moderates selected outcomes; these analyses will be interpreted as hypothesis generating rather than confirmatory causal tests.

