## Methods

### Study Design

This study will use a 3-arm, parallel-group, single-center randomized controlled trial design. Assessments will be conducted at baseline (T0), immediately after the intervention (T1, week 6), and at a 1-month follow-up (T2, week 10) to evaluate short-term maintenance of effects. The primary planned comparison is the experimental group vs the active control group, which isolates the added value of the social layer over a matched solo VR intervention. Comparisons involving the waitlist control are secondary. This protocol was prepared in accordance with the SPIRIT (Standard Protocol Items: Recommendations for Interventional Trials) guidelines.

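### The random-intercept-only model fixes one variance and one correlation across visits, so the type I error of the primary T1 and T2 contrasts rests on a doubtful and unnecessary assumption

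*Protocol article*

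**What the plan says.** The analysis text stands under Data Management in the protocol article. It sets out the fixed effects ("linear mixed-effects models will be used to examine group, time, and group×time effects on BDI-II and BAI scores") and the dependence between visits ("Separate models will be fitted for depression and anxiety outcomes, with participant-level random intercepts to account for repeated measures over time"). It names no random slope, other residual structure or robust standard error. The role of baseline is left open: "baseline symptom severity will be considered in model specification as appropriate". On the tests that matter it says: "The primary planned contrasts will compare the experimental group with the active control group at T1 and T2".

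The same model carries the missing-data strategy, with "maximum likelihood estimation in mixed models as the primary approach". Missing-data assumptions are to be examined, and multiple imputation is a sensitivity analysis where appropriate. The Sample Size Calculation section expects 20% to 30% attrition.

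There are three measurement times: "All self-report and fitness measures will be collected at T0, T1, and T2". Study Design puts T1 at week 6, when the intervention ends, and T2 at week 10. The inclusion criteria require a BDI-II of 14 to 28 or a BAI of 8 to 25.

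**The concern.** A participant intercept with independent, equal-variance residuals implies compound symmetry: every visit has the same variance and every pair of visits the same correlation. Three features of the design argue against it.

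- T0 and T2 are ten weeks apart with the whole intervention between them. T1 and T2 are four weeks apart with none. The T1-T2 correlation is therefore likely to be the highest and the T0-T2 correlation the lowest.
- Response to treatment can vary between people after T0 and so change the variance at T1 and T2.
- Entry selects on T0 scores, which may narrow the spread at T0 but not later.

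If the assumption fails, the model applies an averaged variance to each contrast, and the standard errors at T1 and T2 can be too small or too large. Likelihood estimation under missing-at-random also relies on the covariance being right, because observed T1 scores inform the missing T2 scores through it.

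**Working it through.** **Inputs.** From the protocol: three visits, three arms at 1:1:1, 110 recruited, 20% to 30% attrition, nominal alpha .05, random intercept only. Not in the protocol, hence assumed: all SDs and correlations. Correlations are listed as T0-T1 / T0-T2 / T1-T2.

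**Formula.** With balanced complete data, the random-intercept model uses the mean of the three pairwise difference variances for a change contrast, and the mean of the three visit variances for a level contrast (between-group difference at a visit). The SE ratio is sqrt(model variance / true variance), and the actual error is 2 × (1 − Φ(1.96 × ratio)).

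**Nominal figure.** With equal SDs and equal correlations every ratio is 1 and the error is 5.0%, so the plan's .05 is met when compound symmetry is true.

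**T0 as a response, change contrast, equal SDs.** Difference variances are 2(1 − correlation) in SD² units.

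| Correlations | T0-T1, T0-T2, T1-T2 difference variances | Mean | T1 ratio, error | T2 ratio, error |
|---|---|---|---|---|
| 0.6/0.5/0.7 | 0.8, 1.0, 0.6 | 0.800 | 1.000, 5.0% | sqrt(0.800/1.0) = 0.894, 8.0% |
| 0.5/0.4/0.7 | 1.0, 1.2, 0.6 | 0.933 | 0.966, 5.8% | sqrt(0.933/1.2) = 0.882, 8.4% |

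**T0 as a response, level contrast.** With equal SDs the ratio is 1 whatever the correlations: 5.0%. If the T0 SD is k times a common later SD, the ratio is sqrt((k² + 2)/3). Simulating the entry rule gave k of 0.93 to 0.95 for BDI-II and 0.85 to 0.88 for BAI.

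| k | Ratio | Error |
|---|---|---|
| 0.95 | 0.984 | 5.4% |
| 0.93 | 0.977 | 5.5% |
| 0.88 | 0.962 | 5.9% |
| 0.85 | 0.953 | 6.2% |

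**Baseline as a covariate, T1 and T2 as responses, equal SDs.** Residual variances are 1 − r², and the model uses their mean.

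- 0.6/0.5/0.7: T1 0.64, T2 0.75, mean 0.695. T2 error 5.9%, T1 error 4.1%.
- 0.5/0.4/0.7: T1 0.75, T2 0.84, mean 0.795. T2 error 5.7%, T1 error 4.4%.

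**Other patterns.** SDs falling 9/8/7 give a mean variance of (81 + 64 + 49)/3 = 64.67 against 49 at T2, a ratio of 1.149 and a level-contrast error of 2.4%. SDs rising 6/8/9 give 60.33 against 81, a ratio of 0.863 and 9.1%. A more extreme 4/8/9 gives 11.1%.

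**Simulation (N = 110, three arms, REML random intercept).** SDs 6/8/9 with 0.6/0.5/0.7 and no dropout gave T2 errors of 9.1% (level) and 8.0% (change), in line with the closed form. Dropout of 25% was then added:

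- Dependent on T1 in the same way in all arms: T2 bias about zero (at most 0.12 points).
- Dependent on T1 in opposite directions in the two VR arms: T2 bias of about −0.7 to −1.5 points where T0 was narrower and the T2 SD was 9, with error up to about 17%. It was only about −0.1 with equal SDs and 0.6/0.4/0.6.
- True compound symmetry: no bias.

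**Same data patterns, unstructured covariance (1,000 runs each).** T2 error was about 3% to 5% without dropout and 4.5% to 6.2% with 25% dropout. T2 bias lay between −0.11 and +0.18 points, within simulation noise, including under opposite-direction dropout.

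**The case against.** A reader might infer that the T2 test in this trial runs at 7% to 9%. The documents do not support that. They give no SD by visit and no correlation, and the higher figures need either a change contrast with T0 as a response or clearly rising SDs. The sentence on planned contrasts reads most directly as a difference at each visit, which holds 5.0% under equal SDs. The entry rule needs only one scale in its window, so the narrowing at T0 is modest. With baseline as a covariate most of the excess goes. The direction is not fixed either.

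A second tempting inference is that likelihood handling of dropout will bias the T2 result. That took a particular combination, and the plan does examine missing-data assumptions and offers multiple imputation as a sensitivity analysis.

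It can also be said that the article is condensed, that naming a random intercept does not exclude a richer residual structure, and that a fuller analysis plan may add one.

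All this limits the size. Two things remain. The dependence model is stated, not omitted, and the primary handling of attrition rests on it. The change reading also has support, since Primary Outcomes defines the outcome as change in severity and Sample Size Calculation refers to a group-by-time comparison. A sensitivity analysis does not repair the primary test.

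**Conclusion.** The point holds as a conditional robustness defect and should be corrected. The type I error of the primary contrasts depends on compound symmetry, which this design makes doubtful and which the analysis does not need.

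Under the assumed decaying correlations, the T2 error is about 8.0% to 8.4% for a change contrast and 5.7% to 5.9% with baseline as a covariate. A level contrast gives 5.0% with equal SDs and about 5.4% to 6.2% under the simulated entry-rule SD ratios. It is exactly 5% if compound symmetry is true and can be conservative, to about 2.4%, if SDs fall over time. Bias at T2 is a concern only if T1-dependent dropout differs by arm and the covariance is also misspecified. All sizes rest on assumed SDs and correlations and on reading the residuals as independent with equal variance.

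**What to change.** In Data Management, replace the random-intercept covariance with an unstructured covariance across the modelled visits (3×3 if T0 is a response, 2×2 for T1 and T2 if baseline is a covariate). Fit it by REML with Kenward-Roger degrees of freedom, and name heterogeneous Toeplitz as the fallback if it does not converge. The random-intercept model may stay as a sensitivity analysis.

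The cost is a change of wording and a software option. A 3×3 unstructured matrix has six parameters against two, so at most four more, which is negligible with 77 (110 × 0.7) to 110 participants. According to Results, no participant had been enrolled as of April 2026, so the change can be made before any data exist.

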### Interventions

#### Experimental Group: VR Social Musical Exergame

Participants in this arm will engage in the VR intervention twice a week for 45 minutes over 6 weeks. Prior to the first intervention session, all participants in VR conditions (experimental group and active control group) will complete a 15-minute familiarization session using a neutral, nontherapeutic VR environment to reduce initial novelty effects and identify individuals who may experience significant cybersickness. Waitlist control participants will receive a brief (5-minute) VR demonstration to partially equalize technology exposure. The experimental condition is conceptualized as a bundled social VR musical exergame designed to support autonomy, competence, and relatedness simultaneously.

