#### Relatedness and Social Layer

Participants interact in multiuser virtual rooms for collaborative and competitive team tasks, with real-time voice chat enabled to support communication and social connection. Each session will include a minimum of 10 minutes of structured collaborative or competitive team tasks and at least 5 minutes of open voice chat interaction with coparticipants. The social manipulation therefore comprises multiple elements, including peer communication, collaboration, and structured social comparison. Accordingly, the trial tests the added value of this bundled social layer rather than the isolated effect of any single social feature.

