#### Active Control Group: VR Solo Musical Exergame

This group will engage in a VR exergame with the same frequency, duration, exercise intensity, game content, and music design as the experimental group. However, all social features will be disabled. This condition is designed to preserve autonomy and competence support while removing the bundled social layer, and it serves as the primary comparator for testing the unique contribution of social interaction.

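### The social arm is grouped into shared rooms, but the stated primary model has no room term; if room-mates' outcomes are positively correlated, the standard error of the primary contrast is understated.

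*Protocol article*

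**What the plan says.** Under Relatedness and Social Layer, the protocol article describes how the social arm works: "Participants interact in multiuser virtual rooms for collaborative and competitive team tasks, with real-time voice chat enabled to support communication and social connection". The dose of contact between coparticipants is fixed there too: "Each session will include a minimum of 10 minutes of structured collaborative or competitive team tasks and at least 5 minutes of open voice chat". The Experimental Group section gives the schedule: "Participants in this arm will engage in the VR intervention twice a week for 45 minutes over 6 weeks", which is 2 × 6 = 12 shared sessions.

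For the active control, the article says "all social features will be disabled". The Randomization and Blinding section allocates individual participants 1:1:1.

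The analysis paragraph, printed under Data Management, fits separate linear mixed models to BDI-II and BAI "with participant-level random intercepts to account for repeated measures over time". It adds fixed covariates: "Gender and primary presenting concern (the stratification variables) will be included as covariates". The primary contrasts are experimental versus active control at T1 and T2. That paragraph names no room or group effect, cluster-robust standard error or partially nested structure. The Sample Size Calculation section gives no ICC and no design effect. The seven limitations in the Discussion do not include dependence between room-mates.

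**The concern.** A participant random intercept absorbs correlation between one person's repeated scores. It does nothing for correlation between different people who shared a room. Here the treatment is the contact between participants, and the trial's hypothesis is that this contact changes symptoms. If peers do affect one another, room-mates' BDI-II and BAI scores may well move together, so the mechanism under test is also a plausible source of dependence.

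The grouping falls on one side of the comparison that the article names as primary. Ignoring a positive within-room correlation would shorten the confidence interval for that contrast and reject a true null hypothesis more often than the nominal 5%. Part of this cannot be repaired later: if room membership is not recorded during the sessions, no subsequent analysis plan can model it.

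**Working it through.** **The plan's own figure.** The article states 90 participants for 80% power at f = 0.25 and alpha .05, with 110 recruited. It does not say which G*Power test or what correlation between time points was used. Noncentral-F calculations for one-way, between-factors and group-by-time designs (2 or 3 groups, 2 or 3 time points, correlation 0 or 0.5) gave totals from 28 to 158, none of them 90. A 2-group, 3-time between-factors test gives 90 only with an unstated correlation of about 0.55. That is a separate matter. What counts here is that the article states no clustering allowance for this figure.

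**Inputs.**
- From the article: 12 shared sessions in the social arm, an ungrouped comparator, individual 1:1:1 randomization, participant-level random intercepts.
- Assumed, because the article does not give them: room size m, within-room ICC, equal arms, a single time point, fixed rooms.

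**Formulas.**
1. Design effect in the social arm: DE = 1 + (m − 1) × ICC. In the solo arm it is 1.
2. True over model-based standard error of the arm difference: R = √[(1 + DE)/2].
3. Actual type I error of a nominal 5% test: 2 × [1 − Φ(1.96/R)].
4. Power with a valid standard error, if nominal power is 80%: Φ[(1.96 + 0.842)/R − 1.96].

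**Worked case, m = 4, ICC 0.10.** DE = 1 + 3 × 0.10 = 1.30. R = √(2.30/2) = √1.15 = 1.072. Type I error = 2 × [1 − Φ(1.96/1.072)] = 6.8%. Power = Φ(2.802/1.072 − 1.96) = 74%. Thirty social-arm completers carry the information of 30/1.30 = 23.

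| Room size | ICC | DE | SE ratio R | Type I error | Power if nominal 80% |
|---|---|---|---|---|---|
| any | 0 | 1.00 | 1.000 | 5.0% | 80% |
| 2 | 0.05 | 1.05 | 1.012 | 5.3% | 79% |
| 4 | 0.05 | 1.15 | 1.037 | 5.9% | 77% |
| 4 | 0.10 | 1.30 | 1.072 | 6.8% | 74% |
| 6 | 0.10 | 1.50 | 1.118 | 8.0% | 71% |
| 10 | 0.10 | 1.90 | 1.204 | 10.4% | 64% |

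**Simulation check.** A two-sample test that ignores rooms, with 30 per arm and fixed rooms, gave type I errors of 5.2% (m = 2, ICC 0.05), 7.8% (m = 6, ICC 0.10) and 10.1% (m = 10, ICC 0.10), close to the formula. With m = 5, fixed rooms gave 6.3% at ICC 0.05 and 7.3% at ICC 0.10. Reshuffling membership at each of 12 sessions gave 5.9% and 7.3%. On these assumptions, changing rooms does not remove the inflation.

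**Cost of a valid interval.** Take 30 completers per arm, one time point, and Satterthwaite degrees of freedom df = (1 + DE)² / [DE²/(K − 1) + 1/29], where K = 30/m rooms. The reference is the 58-df critical value, 2.002.
- m = 4, ICC 0.10: K = 7.5, df ≈ 18, critical value 2.101. Interval ratio 1.072 × 2.101/2.002 = 1.13.
- m = 6, ICC 0.10: K = 5, df ≈ 10.5, critical value 2.215. Interval ratio 1.118 × 2.215/2.002 = 1.24.

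**The case against.** A reader might infer that the standard errors are too small as a matter of fact, because outcomes within a room are correlated by design. The documents do not support that. Contact is by design; correlation of BDI-II or BAI scores is not. It is a reasonable expectation, but the article gives no ICC. The social layer includes competition and social comparison, and a negative within-room correlation would reverse the bias. At ICC 0 there is none, and for pairs at ICC 0.05 it is about 1% of the standard error.

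It can also be said that the quoted phrase explains only how repeated measures are handled, that a journal article condenses, and that a room term could sit in an unseen analysis plan. This stands in part: the article does not exclude a room term. But it states a random-effects structure and covariates for the primary model, and as stated the model does not match the design described a few sections earlier.

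No passage says that rooms keep the same members, whereas the design-effect formula assumes that they do. This stands as a limit on the formula, though the reshuffling check gave similar inflation.

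Finally, the solo arm may not be wholly independent either. Session facilitators check in with participants before and after each VR session (Safety Monitoring and Adverse Events), so a facilitator effect could reach both VR arms. Setting clustering to zero outside the social arm is therefore one defensible choice, not the only one.

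**Conclusion.** The point holds in conditional form. The design is partially nested, the stated primary model names only participant-level random intercepts, and the sample size section states no allowance for clustering. If within-room correlation is positive, the primary contrast's standard error is understated and its type I error exceeds 5%.

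The size rests on assumed room sizes and ICCs. It runs from nothing at ICC 0, through 5.3% to 6.8% for rooms of 2 to 4 at ICC 0.05 to 0.10, to 8.0% for rooms of 6 at ICC 0.10, and higher for larger rooms or ICCs. The facts about design and model are firm; the direction and size of the consequence are not. It should be corrected before enrollment, chiefly because room membership has to be captured as the sessions happen.

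**What to change.** 1. Log the room ID and the co-participants present at every social-arm session. The VR software already captures behavioral data continuously, so this should be a small addition. Room scheduling need not change: requiring stable rooms would alter how the intervention is delivered and could conflict with the flexible scheduling promised under Sample Size Calculation to limit attrition.
2. Prespecify a primary model with a room random effect in the experimental arm, in multiple-membership form if rooms change, with small-sample degrees of freedom such as Kenward-Roger.
3. Report the estimated ICC with its uncertainty.
4. State under Sample Size Calculation that the 80% and approximately 70% power figures assume no within-room correlation.

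The cost is a modest amount of extra analysis and some precision. About 37 people (110/3) are randomized to the arm, so rooms of 4 give about 9 rooms; 30 completers in rooms of 6 give 5. The room variance will be poorly estimated. Intervals widen by roughly 13% (rooms of 4) to 24% (rooms of 6) at ICC 0.10 under the assumptions above, and by more if rooms are larger or the ICC is higher.
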